### **9.3 Statistical analysis plan**

#### **9.3.1 Summary of baseline data and flow of patients**

All analysis and reporting will be in line with Consolidated Standards of Reporting Trials (CONSORT) guidelines. Primary analyses will be conducted on an intention-to-treat (ITT) basis. A full statistical analysis plan will be developed and agreed by the trial steering committee (TSC) prior to undertaking the analyses of the main trial.

Descriptive statistics will be used to determine whether there are imbalances at baseline between treatment groups and will inform any later sensitivity analyses where appropriate additional adjustment will be performed. Patient-reported outcome scores based on standardised questionnaires will be calculated based on the developers' scoring manuals and missing and erroneous items will be handled according to these manuals. Continuous measures will be presented as means and standard deviations or medians and ranges depending on their distribution. Categorical data will be presented as frequencies and proportions.

#### **9.3.2 Primary outcome analysis**

The primary endpoint in this study is a composite outcome of non-cancer death or hospital admission for infection or cardiovascular event by a minimum of 32 to maximum of 91 months follow-up. We will compare the distribution of time-to-events between the two groups using Kaplan-Meier curves and log-rank test. We will use Cox's proportional hazard model - or an alternative flexible parametric model to compare the two groups if the assumption of proportional hazards is not met - to compare the time-to-events between the two groups with adjustment for stratification variables.

A per protocol analysis will be performed with patients censored at the time of discontinuation of allocated treatment (including receipt of a kidney transplant, transition to home dialysis, receipt of the alternative form of HD/HDF on the last session of two sequential months, and patient choice to come off allocated treatment), with adjustment made for baseline characteristics. Recognising biases inherent to per protocol analyses when compliance is not random, we will also consider appropriate alternative causal inference approaches to estimate the treatment effect in compliers.

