#### **4 TRIAL DESIGN**

A non-blinded, randomised, parallel group, controlled trial comparing high-volume HDF (aiming for 21+L of substitution fluid adjusted to body surface area) against high-flux HD, randomised 1:1 and stratified by site, age (18-64 and 65+) and residual renal function (urine volume <100mL/day and 100+mL/day (26-28)). The primary analysis will be intent to treat using proportional hazards regression and adjusting for variables used to stratify the randomisation.

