**Table 1 Summary of baseline data collection for the randomised controlled trial**

|                     |                                                                                                                                                                                                                                                                                                                             |
|---------------------|-----------------------------------------------------------------------------------------------------------------------------------------------------------------------------------------------------------------------------------------------------------------------------------------------------------------------------|
| Demographics/social | Age, sex, ethnicity, marital status, education level, smoking history.                                                                                                                                                                                                                                                      |
| Clinical            | Primary renal disease, date first seen by nephrologist, RRT treatment history, co-morbidities, dietary restrictions, prescribed medication (including erythropoiesis stimulating agents and phosphate binders), 24-hour urine volume (within the 6 weeks preceding randomisation).                                          |
| Resource use        | Day case and inpatient hospital admissions (including surgical procedures performed), nursing home/residential home days/hospice days, other hospital outpatient services and primary care & community services in the last 6 months.                                                                                       |
| Laboratory          | Creatinine, urea, Kt/V, urea reduction ratio, albumin, haemoglobin, haematocrit, mean corpuscular volume, sodium, potassium, bicarbonate, corrected calcium, phosphate, c-reactive protein, intact parathyroid hormone, total cholesterol. (From the date of the study visit or the closest date prior to the study visit.) |
| Physical assessment | Height, weight, blood pressure, heart rate.                                                                                                                                                                                                                                                                                 |

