#### **9.4 Subgroup analyses**

We will conduct pre-planned subgroup analyses to investigate any differential effects according to baseline urine volume (a surrogate for residual kidney function), diabetic status, line, weight at baseline, age and the experience of sites in achieving high-volume HDF. Subgroup analyses will be conducted by including an interaction term between allocated treatment and baseline characteristic in regression models then using the likelihood ratio test comparing this model with one excluding the interaction term. Urine volume and age will be included in the model as continuous variables.

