#### **9.5 Adjusted analysis**

All analyses will be adjusted for stratification variables and, in the case of patient-reported outcomes, we will also adjust for the value of the outcome pre-randomisation. For all statistical models used the underlying assumptions will be checked using standard methods. If assumptions are not valid then alternative methods of analysis will be sought.

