## **10 DATA HANDLING**

### **10.1 Data collection tools and source document identification**

Baseline data will be entered directly into a case report forms (CRF) and sent securely (by post or electronically) no more than 4 weeks after the baseline visit to the CTU for entry into the database. Baseline patient questionnaires (PQs) will be administered by the research staff at the baseline visit and returned to the CTU for entry into the database; thereafter, PQs will be sent out 6-monthly by the CTU to the patient with an enclosed cover letter signed by the site principal investigator and research nurse and returned directly to the CTU. If a patient questionnaire is not returned, up to 2 reminders will be sent. Where appropriate questionnaires can be administered by telephone from the CTU to get responses from the patient to the EQ5D questions.

Standardised tools are being used:

- Co-morbidity: Davies co-morbidity Score (52) & Charlson co-morbidity index (53)
- Quality of life: EQ-5D-5L (54), and DSI (55).

A central administrative database will be set up by BTC that prompts the CTU when PQ forms are due.

PIs must keep records of all participating patients (sufficient to link records e.g., CRFs and hospital records), all original signed informed consent forms and copies of the CRF pages.

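### The primary Cox model adjusts only for the stratification variables; pre-specifying prognostic covariates already collected at baseline would add a modest amount of power

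*Protocol*

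**What the plan says.** The covariates of the primary model are fixed in three places in the Protocol. Section 4 plans proportional hazards regression "adjusting for variables used to stratify the randomisation". Section 9.3.2 specifies the Cox model "with adjustment for stratification variables". Section 9.5 states "All analyses will be adjusted for stratification variables", adding only the pre-randomisation value for patient-reported outcomes. The stratifiers are given in section 4: "randomised 1:1 and stratified by site, age (18-64 and 65+) and residual renal function", the last split at 100 mL/day of urine.

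Other baseline information is collected or planned for use elsewhere:

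- Table 1 lists "Age, sex, ethnicity, marital status, education level, smoking history", and also co-morbidities and a 24-hour urine volume.
- Section 10.1 names two comorbidity instruments, the first being "Co-morbidity: Davies co-morbidity Score" and the second the Charlson index.
- Section 9.4 uses diabetic status as a subgroup variable and says of the interaction models: "Urine volume and age will be included in the model as continuous variables".

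The only route to further adjustment of the intention-to-treat analysis is in section 9.3.1, where baseline imbalances "will inform any later sensitivity analyses where appropriate additional adjustment will be performed".

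**The concern.** In a Cox model, leaving out covariates that strongly predict the event moves the estimated treatment hazard ratio toward 1 while its standard error hardly changes, so the test loses some power. Age in years, urine volume, diabetes and comorbidity plausibly predict death or admission for cardiovascular disease or infection in dialysis patients. The plan holds these data and uses some of them in subgroup models, but gives the primary comparison only coarse versions of two of them and nothing on diabetes or comorbidity.

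The trigger for extra adjustment in section 9.3.1 is also a poor one. In a randomised trial, covariates are better chosen beforehand for prognostic strength than afterwards because the arms happen to differ.

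What is at stake is some precision in the primary result and in the mortality outcomes, which section 9.3.3 analyses in the same way.

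**Working it through.** **1. Reproduce the plan's figure (section 9.1).** Inputs: 3-year event proportions 62.5% (HD) and 54.1% (HDF), 90% power, 5% significance (taken as two-sided), 801 events, 10% loss.

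- HR = ln(0.459)/ln(0.375) = 0.794.
- (1.960 + 1.282)² = 10.507.
- Freedman: 10.507 × [(1 + 0.794)/(1 − 0.794)]² = 797 events with the unrounded HR.
- Schoenfeld: 4 × 10.507/(ln 0.794)² = 790 events.

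Both are close to 801, so the stated figure is reproduced. It is an unadjusted calculation.

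Participants: 801/0.583 = 1,374, and 1,374/0.9 = 1,527 as stated. I used 1,374. The 1,348 in section 9.1 does not fit its neighbours (1,348/0.9 = 1,498), which is a separate matter.

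**2. Simulate the planned and the enlarged model.** There were 3,000 trials per scenario, each with 1,374 participants, 1:1 allocation and censoring at 3 years. Marginal event proportions were calibrated to 62.5% and 54.1%, giving about 801 events. All models were fitted to the same data. The enlarged model keeps the stratifiers and adds continuous age, continuous log urine volume, diabetes and a comorbidity score.

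The documents give no prognostic strengths, so these are assumptions:

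| Log hazard ratio | Weak | Moderate | Strong |
|---|---|---|---|
| Age, per SD | 0.15 | 0.30 | 0.45 |
| Log urine volume, per SD (protective) | 0.10 | 0.15 | 0.20 |
| Diabetes | 0.15 | 0.30 | 0.40 |
| Comorbidity score, per unit | 0.10 | 0.20 | 0.35 |
| Resulting SD of log hazard | 0.28 | 0.49 | 0.73 |

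Also assumed: age mean 64 and SD 15; half below 100 mL/day; 40% diabetic; comorbidity mildly related to age and diabetes; 20 sites with a log-hazard SD of 0.15.

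**3. Results.** Where two figures appear, one is the proportion of significant trials and the other is Φ(mean z − 1.96).

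| | Weak | Moderate | Strong |
|---|---|---|---|
| Power, unadjusted | 89.9-90.0% | 90.3-90.4% | 91.0% |
| Power, site + two dichotomies | 90.9% | 92.2-92.5% | 94.1-94.2% |
| Power, enlarged model | 91.5-91.8% | 94.5-94.7% | 97.6-97.9% |
| Gain over planned model (points) | 0.6-0.9 | 2.0-2.5 | 3.4-3.8 |
| Mean z, planned → enlarged | 3.293 → 3.334 | 3.397 → 3.559 | 3.535 → 3.945 |
| Ratio of information, (z₂/z₁)² | 1.025 | 1.098 | 1.245 |
| Estimated HR, planned → enlarged | 0.790 → 0.787 | 0.784 → 0.774 | 0.776 → 0.752 |

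The information ratios are the 2%, 10% and 24% more events. The simulation error of a single power figure is about √(0.909 × 0.091/3,000) = 0.5 points. The comparisons are paired, so the differences are better determined than that.

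Replacing only the two dichotomies by continuous terms gains 0.2, 0.8 and 1.4 points. Most of the benefit therefore comes from diabetes and comorbidity.

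**4. Longer follow-up.** Section 9.3.2 gives 32 to 91 months, while the Trial Summary gives the outcome within 3 years. Assume uniform entry, constant hazards and 1,550 × 0.9 = 1,395 participants.

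- Monthly hazards: −ln(0.375)/36 = 0.02725 (HD) and −ln(0.459)/36 = 0.02163 (HDF).
- Event proportion: 1 − (e^(−32λ) − e^(−91λ))/(59λ) = 0.792 (HD) and 0.717 (HDF).
- Events: 1,395 × (0.792 + 0.717)/2 ≈ 1,053.
- z = √1,053/2 × 0.2308 = 3.744, so power without extra covariates is 96.3%.
- Multiplying z by √1.025, √1.098 and √1.245 gives 96.6%, 97.5% and 98.7%. The gains are about 0.4, 1.2 and 2.4 points, taking the 3-year information ratios to carry over.

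**The case against.** Sections 4, 9.3.2 and 9.5 agree with each other and with the randomisation in section 7.2. Adjusting for the stratifiers is a recognised, pre-specified choice, and simulated power under it is above target. That all stands, and it is why this is a matter of efficiency.

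Several stronger readings are tempting but not supported:

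- **The trial is underpowered.** It is not. The planned model gives about 91-94% at 801 events, and power is about 96% with the longer follow-up.
- **The planned test is biased or invalid.** It is not. The shift in the hazard ratio reflects a different conditioning set (non-collapsibility of the hazard ratio).
- **The primary result is open to selection through section 9.3.1.** That section confines imbalance-driven adjustment to sensitivity analyses, and section 7.3 blinds the analysing statistician.
- **The protocol commits to dichotomised age and urine volume.** That is the natural reading, but no functional form is written, and an SAP could enter both as continuous. This part matters least, since undoing the dichotomies alone adds at most 1.4 points.
- **The change costs nothing.** It needs no new data, but it needs a missing-data rule and it conditions the hazard ratio on more covariates.

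That an SAP may fill in detail does not fully answer the point. The protocol names the covariate set three times, so an SAP that added diabetes and comorbidity would depart from it and, under section 9.9, the protocol wording should be aligned.

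**Conclusion.** The point holds as an efficiency improvement, not as an error in the plan. The primary adjustment is limited to the stratification variables although stronger prognostic information is available at baseline. Adding it raised power in every scenario examined, from under 1 point to just under 4 points at about 801 events. With 32-91 months of follow-up the gain is roughly 0.4 to 2.4 points.

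The direction is secure. The size rests on assumed covariate effects, since the documents give none, and chiefly on how well diabetes and comorbidity predict the composite. If those effects are weak, the benefit is negligible. The stated 90% power is met either way.

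**What to change.** Before any unblinded analysis:

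- In sections 9.3.2 and 9.5, with section 4 aligned, state that the primary Cox model adjusts for site, age (continuous), urine volume (continuous), diabetic status and one comorbidity score named in advance, for example the Davies score.
- Give a simple rule for missing baseline values, such as imputation from other baseline data without reference to allocation or outcome. Section 7.1 makes randomisation wait for the urine measurement, so age and urine volume should be nearly complete.
- Keep the model with the stratification variables only as a sensitivity analysis.
- In section 9.3.1, choose covariates for any additional adjustment by prognostic value, not by observed imbalance.

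The cost is protocol and SAP wording, with no new data and about four extra terms against 801 events. There are two small downsides: a few missing baseline values need handling, and the hazard ratio becomes conditional on more covariates (0.784 to 0.774 in the moderate scenario), which the report should say.

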#### **9.3.3 Secondary outcome analysis**

The secondary outcomes of all-cause mortality, non-cancer mortality, cardiovascular mortality, infection mortality will be analysed and reported in a similar manner to the primary outcome as described in section 9.3.2.

Cardiovascular and infection-related hospitalisations and MRSA and MSSA infections are all recurrent events and analyses of such outcomes should account for informative censoring due to death. We will therefore use joint frailty models (JFMs) as these simultaneously analyse recurrent events (infections or hospitalisations) and time to death while estimating distinct hazard ratios. Appropriate repeated measures regression models for patient-reported outcomes will be chosen based on the distribution of the data and will adjust for stratification variables and values of the outcome at the time of randomisation. A similar repeated measures regression approach will be taken to the following other repeated measure outcomes: time to recover after each dialysis session, haemoglobin levels, erythropoiesis stimulating agent dose, calcium levels, phosphate levels, PTH levels, albumin levels, and phosphate binder dose.

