## STUDY PROTOCOL

### The High-volume Haemodiafiltration vs High-flux Haemodialysis Registry Trial

#### 1 BACKGROUND

End-stage kidney disease (ESKD) affects ~55,000 people in the UK, with ~7,000 newly affected people each year (1, 2). It ranks among the most severe of the chronic non-communicable diseases. The survival probability at one, three and five years is around 90, 70 and 50%, respectively (3). Morbidity is high, with dialysis patients in the UK admitted to hospital on average ~1.5-2.0 times per year and spending ~15 days in hospital per year (4). Quality of life on dialysis is also well below that of the general population (5). There is therefore an unmet and urgent need to improve ESKD patient treatment.

Renal replacement therapy (dialysis or transplantation) is necessary when approximately 90% of kidney function is lost. Currently ~90% of existing dialysis patients are on some form of haemodialysis (HD) or haemodiafiltration (HDF) (2). Although HD and HDF can be performed at home, the majority is performed in-centre.

HD relies on 'diffusion' – molecules at high concentrations in the blood pass across a membrane in an artificial kidney or dialyser to reach low concentrations in the dialysate fluid. At first, the pores in these membranes had to be small to avoid the loss of proteins and this meant that only small-sized toxic molecules could leave the blood. As technology advanced, these pores became larger and more complex/ asymmetrical, making it easier for larger toxic molecules to leave the blood whilst essential proteins are retained. These "high-flux" membranes are now recommended as standard practice in the UK (6). Even with these high-flux membranes, however, only the equivalent of 10-15% of toxin removal can be achieved within the timing/ frequency of a fairly standard dialysis prescription (i.e. 4 hours three times a week) (7).

HDF is similar to HD in that it uses diffusion to clean the blood (see above), but at the same time it uses 'convection' – a process that pulls fluid across the membrane, taking any dissolved solutes with it. When large volumes of fluids are pulled across the membrane (more than 23L per treatment session) it is considered 'high-volume' HDF. Adding convection achieves more efficient removal of middle-sized water soluble and even protein bound toxic molecules that cause cardiovascular damage, impaired immunity and other organ damage (8). This could explain why meta analyses of

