### **7.6 Long term follow-up assessments**

Follow up will continue for a minimum of 32 months and a maximum of 91 months. It will be undertaken through a combination of 6-monthly patient questionnaires and linkage to routine healthcare databases

such as the UK Renal Registry, Hospital Statistics (for England/ Wales/ Scotland and/or Northern Ireland), Civil Registration (**Table 2**). Only data that are collected as part of routine care will be collected. Paper and electronic (web portal) options will be offered to patients for patient questionnaire completion.

Adherence to the protocol will be monitored through UK Renal Registry treatment modality returns and contact with dialysis units throughout the follow up. As the UK Renal Registry follows all patients on RRT in the UK, patients should not be lost to follow-up unless they move to another country.

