## **9 STATISTICS AND DATA ANALYSIS**

### **9.1 Sample size calculation**

We anticipate that at 3 years of follow-up 65% of patients on HD will have experienced our composite endpoint and we plan to detect a HR of 0.75. This effect size was agreed to be clinically significant at an investigator meeting involving patients and health care professionals. We assume any effect will be attenuated by (i) cross-over between arms (15% HD to HDF & 5% HDF to HD) and (ii) participants being allowed to take part in other trials simultaneously. To optimise recruitment and avoid excluding eligible patients because they are already participating /want to participate in other trials, an additional adjustment has been made that assumes up to half of patients in both groups will take part in another trial that assigns half of these to an intervention that reduces our composite end-point (HR=0.9), the anticipated proportion experiencing an event on HD will be 62.5% (37.5% surviving event-free) & on HDF it will be 54.1% (45.9% surviving event-free) giving a revised HR of 0.79. The number of events required to detect this difference with 90% power and a 5% significance level is 801, which requires 1348 participants in total. The primary analysis will be intention to treat and to avoid informative censoring participants will not be censored for transplant (10). Allowing for 10% loss to follow-up for other reasons we require 1527 participants and will recruit 1550.

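### Kaplan-Meier curves for cardiovascular and infection mortality would overstate the risk of dying from each cause; cumulative incidence curves should replace them

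*Protocol*

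**What the plan says.** Section 9.3.3 of the protocol groups four mortality outcomes and states that "all-cause mortality, non-cancer mortality, cardiovascular mortality, infection mortality will be analysed and reported in a similar manner to the primary outcome", with a reference back to section 9.3.2. That section begins: "We will compare the distribution of time-to-events between the two groups using Kaplan-Meier curves and log-rank test". It then specifies a Cox model adjusted for the stratification variables, "or an alternative flexible parametric model to compare the two groups if the assumption of proportional hazards is not met".

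The next paragraph of 9.3.3 turns to recurrent hospitalisations and infections. It says that "analyses of such outcomes should account for informative censoring due to death" and adopts joint frailty models for them. The protocol makes no matching provision for cause-specific death: it nowhere mentions competing risks, cumulative incidence estimation or a subdistribution hazard.

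Two other statements bear on the size of the effect. Section 1 reports: "The survival probability at one, three and five years is around 90, 70 and 50%, respectively". Section 7.6 says: "Follow up will continue for a minimum of 32 months and a maximum of 91 months".

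**The concern.** A patient who dies of cancer, or after withdrawing from dialysis, can no longer die of a cardiovascular cause. A Kaplan-Meier curve for cardiovascular death treats that patient as censored, as though still able to have the event later. Its complement therefore describes a hypothetical population in which nobody dies of anything else. In a population where about half are dead at 5 years, that is far from the risk patients actually face.

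What is at stake is the vertical scale of the secondary mortality figures and any risk read from them. Curves drawn this way for separate causes can add up to more than the all-cause curve on the neighbouring panel, which a reader would find hard to reconcile.

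**Working it through.** **The plan's own figures.** The protocol gives no figure for cause-specific mortality. Its only calculation is the sample size for the composite. Section 9.1 states that "on HDF it will be 54.1% (45.9% surviving event-free) giving a revised HR of 0.79", against 37.5% event-free on HD. Check: ln(0.459)/ln(0.375) = 0.794. At 90% power and two-sided 5%, this needs 790 events (Schoenfeld) to 797 (Freedman), against 801 stated. The figure reproduces closely, and this point does not touch it.

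**Inputs.**
- All-cause survival S(t): 0.70 at 3 years and 0.50 at 5 years (section 1).
- Share s of deaths due to the cause: not in the protocol. Assumed 20-30%, with 10-50% as a wider range, and constant over time.

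**Formulas.** Let the all-cause hazard be λ(t) and the cause-specific hazard s·λ(t).
- Kaplan-Meier with other deaths censored: 1-KM = 1 - exp(-s∫λ) = 1 - S(t)^s.
- Real cumulative incidence: ∫ s·λ(u)·S(u) du = s·(1 - S(t)).

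Only a constant share is needed, not a constant hazard.

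**Worked example, s = 0.25.**
- 3 years: 1 - 0.70^0.25 = 8.5%, against 0.25 × 0.30 = 7.5%.
- 5 years: 1 - 0.50^0.25 = 15.9%, against 0.25 × 0.50 = 12.5%.

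| Time | S(t) | Share s | 1-KM | Cumulative incidence | Excess (points) | Excess (relative) |
|---|---|---|---|---|---|---|
| 3 years | 0.70 | 0.20 | 6.9% | 6.0% | 0.9 | 15% |
| 3 years | 0.70 | 0.25 | 8.5% | 7.5% | 1.0 | 14% |
| 3 years | 0.70 | 0.30 | 10.1% | 9.0% | 1.1 | 13% |
| 5 years | 0.50 | 0.20 | 12.9% | 10.0% | 2.9 | 29% |
| 5 years | 0.50 | 0.25 | 15.9% | 12.5% | 3.4 | 27% |
| 5 years | 0.50 | 0.30 | 18.8% | 15.0% | 3.8 | 25% |

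Over shares of 10-50% the excess is 0.5-1.3 points (9-17% relative) at 3 years and 1.7-4.3 points (17-34% relative) at 5 years.

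**Later follow-up.** Carrying the 5-year average hazard to 91 months gives S = 0.50^(7.58/5) = 0.349. At s = 0.25, 1-KM is 23.1% against 16.3%. This is an extrapolation beyond the last survival figure in the protocol.

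**Additivity.** If three causes take 25%, 25% and 50% of deaths, the 5-year 1-KM values are 15.9%, 15.9% and 29.3%. They add to 61.1%, although only 50% have died.

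**Non-cancer mortality.** The relative excess falls as the share rises: at 5 years it is 34% at s = 0.1, 17% at s = 0.5 and zero at s = 1. Only cancer deaths compete here, so if non-cancer deaths are most deaths the effect is small.

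**The case against.** Several objections have force.

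- **The comparison between arms is sound.** With other-cause deaths censored, the log-rank test and Cox model compare cause-specific hazards, which is a legitimate target. This stands in full. A reader might infer that the cause-specific p-values or hazard ratios are biased. They are not, provided they are labelled for what they are.
- **No absolute risks are promised.** A reader might infer that the published cause-specific risks and risk differences will be too high. Neither 9.3.2 nor 9.3.3 commits to reporting risks or risk differences for these outcomes. The harm arises when 1-KM is read as a probability, which is how such curves are usually read but is not a stated analysis.
- **The text leaves room.** The outcomes are to be handled in a similar manner, not an identical one; detail is deferred to a full SAP, which was not available; and section 9.5 promises alternatives if assumptions fail. But 9.3.3 covers reporting as well as analysis, and the manner it points to names Kaplan-Meier. The fallback in 9.5 is general, and a flexible parametric model answers non-proportional hazards, not competing deaths. This is therefore a method the protocol states, not a gap left to the SAP.
- **The longest horizon flatters the point.** Only patients randomised at the very start of recruitment (1 November 2017) can reach 91 months by 31 May 2025. The conclusion should rest on 3 and 5 years. Five years is well inside follow-up: everyone randomised by 31 May 2020 can reach it, which covers 31 of the 59 recruitment months.
- **Mortality in the trial may be lower.** The survival figures describe ESKD generally, while section 6.2 excludes patients with a predicted prognosis under 3 months or likely insufficient blood flow. If 5-year survival were 70%, not 50%, the 3-year rows of the table would apply at 5 years.
- **The joint frailty models are no contradiction.** They address dependence between recurrent events and death, a different problem. Their use shows awareness that death matters, but it does not make a cause-specific Cox model inconsistent.

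**Conclusion.** The point holds for the curves and for risks read from them. For cardiovascular and infection mortality, 1-KM overstates the real cumulative incidence by about 13-15% relative (roughly 1 point) at 3 years and 25-29% relative (roughly 3-4 points) at 5 years. The excess grows later, but few patients are followed that far. That an overstatement exists is certain whenever other-cause deaths occur. Its size rests on the background survival in section 1 and on an assumed, constant cause share of 20-30%, neither of which is trial data.

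The hazard comparisons, the sample size, the all-cause mortality analysis and the primary conclusion are unaffected. A reader might go further and infer that the primary outcome figure also needs changing because cancer death competes with the composite. The documents do not support that: only cancer deaths before a first event would matter, the composite is expected in 62.5% (HD) and 54.1% (HDF) of patients by 3 years, and nothing in the protocol allows the effect to be sized. This is a correction to secondary reporting, worth making before the data are analysed.

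**What to change.** In section 9.3.3, separate all-cause mortality from the cause-specific outcomes:

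- For cardiovascular and infection mortality, and with a smaller effect for non-cancer mortality, replace Kaplan-Meier curves with Aalen-Johansen cumulative incidence curves by arm, with death from other causes as the competing event.
- Keep the log-rank test and Cox model, and label the result a cause-specific hazard ratio.
- Keep Kaplan-Meier for all-cause mortality.

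A Fine-Gray model is optional; it is not needed to correct the curves. No change to the primary outcome figure is required.

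The cost is a sentence or two of wording, carried into the SAP, and a few lines of code. Section 3.5 already plans cause-specific mortality from the UK Renal Registry, hospital statistics and civil registration, so no further data collection is needed.
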